### Participants

Patients with AECOPD who might meet the inclusion criteria will be screened in the outpatient and inpatient wards, and informed consent will be signed for all patients enrolled in the study. The inclusion criteria are as follows:
A confirmed diagnosis of moderate to very severe AECOPDAge between 40 and 80 yearsSyndrome differentiation meeting criteria of syndrome of external cold and internal fluid, syndrome of phlegm-heat congesting the lung, or syndrome of phlegm-damp amassing in the lungNo participation in other interventional trials in the previous one monthProvision of signed informed consent

The exclusion criteria are as follows:
Pregnant and lactating womenDementia, mental disorders, and reluctant partnersComplicated with heart failure (New York Heart Association [NYHA] Class IV) serious cardiac arrhythmias, or unstable hemodynamicsCurrent respiratory disorders other than COPD (e.g., bronchiectasis, active tuberculosis, pneumothorax, pleural effusion, pulmonary thromboembolism, or neuromuscular diseases affecting respiratory movement function)Combined tumorTreatment outside the hospital for more than 7 daysNeed to carry out invasive mechanical ventilation for respiratory failureComplicated with serious hepatic or renal diseases (liver cirrhosis, portal hypertension, bleeding of varicose veins, dialysis, or renal transplantation)Bedridden for various reasonsAllergic to the used medicine

The rejecting criteria are as follows:
Impacts assessment of effectiveness and safety of the study by seriously violating the research planThere is no way to judge efficacy and safety due to lack of data

### Withdrawal, dropout, and discontinuation

Participants can refuse to participate in the study and follow-up evaluation after enrollment. Other indications for withdrawal are the following situations: (1) development of serious disease (such as acute respiratory failure, acute myocardial infarction, acute heart failure, or stroke) during the observation period; (2) receiving other CM for AECOPD during the observation period; (3) participants who present with serious adverse events (such as death, disability, surgery, or congenital malformations) (4) participants who refuse to continue to participate in the RCT; (5) those lost to follow-up.

### Intervention

#### Health education

The aim of health education is to improve the patient and family awareness of COPD, improve their ability to cope with COPD, and better coordinate treatment and prevention. The substance includes (1) education and supervision and urging patients to stop smoking, guidance to quit smoking, providing means to quit smoking, and striving to reduce passive smoking; (2) mastering the general and certain specific treatment methods, urging patients to adhere to treatment; (3) learning to control CPOD, e.g., with abdominal breathing and shrinkage lip breathing; (4) understanding the timing of hospital visits; (5) avoiding or preventing inhalation of dust, smoke, and harmful gases, etc.

#### Conventional drug

All subjects recruited will receive conventional drug treatment based on the 2017 Global Initiative for Chronic Obstructive Lung Disease (GOLD).

#### Chinese medicine

On the basis of health education and conventional drug treatment, the intervention group will be treated with CM, and the control group will be given a CM placebo. According to traditional CM syndromes, Sanhanhuayin granules are given for the syndrome of external cold and internal fluid, Qingrehuatan granules for the syndrome of phlegm-heat congesting the lung, and Zaoshihuatan granules for the syndrome of phlegm-damp amassing in the lung. Both the CM and the CM placebo granules come in bags, 10 g/bag, which are produced by Jiangyin Tian Jiang Pharmaceutical Co., Ltd. Test results of drug quality were consistent with the required quality standards. Each type of granule will be given orally, twice a day, for 14 days. The dose of the drug is not allowed to be modified.

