## Methods/design

### Objectives

The study objectives are as follows:
Clinical outcome: to test the clinical efficacy of CM for patients with AECOPDSafety evaluation: to evaluate the safety of CM on AECOPD patients.

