### Sample size

The COPD Assessment Test (CAT) will be used as the main outcome. According to previous study results, the average CAT score of AECOPD patients treated by CM is 16.54 ± 5.50 and that of the placebo is 18.33 ± 5.87 [8]. The most reliable estimate of the minimum important difference of the CAT is 2 points [9]. Assuming that α is 0.05 and power is 90%, the two-sided *Z*
_1-α/2_ is 1.96 and *Z*
_1-_β is 1.28. The standard deviation of the first group (σ_1_) is 5.50 and that of the second group (σ_2_) is 5.78, and the clinically meaningful difference (δ) is 2. Based on the formula $$ n=\frac{{\left({{Z_{1-}}_{\alpha}}_{/2}+{Z_{1-}}_{\beta}\right)}^2\times \left({\sigma_1}^2+{\sigma_2}^2\right)}{\delta^2} $$, the sample size in each group is 170. Considering a 10% dropout rate over the course of the study, 189 patients will be enrolled in each group. The total sample size will be 378.

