### Statistical analysis

All data will be analyzed according to the intention-to-treat (ITT) and per-protocol (PP) analyses to reduce deviation. The modified intention-to-treat (mITT) analysis set is a subset of the ITT population and allows the exclusion of some randomized subjects in a justified way. The PP analysis set will include patients who fully complete the trial. The mITT analysis set is used for efficacy and the PP analysis set for safety. Continuous variables will be presented as mean and standard deviation or median and interquartile range according to the Kolmogorov-Smirnov test, and categorical variables as number of patients and proportion.

The Student’s *t* test will be used to compare differences in measurement data. The rank sum test will be used to deal with ranked data, the chi-squared test will be used to analyze categorical data, and the repeated measures analysis of variance (ANOVA) test will be used to analyze multiple measurements at different time-point data. If the effect of the different centers is significant, the Cochran-Mantel-Haenszel (CMH) chi-square test or analysis of covariance (ANCOVA) test is used to correct it. A statistician not involved in data collection will conduct all statistical analyses using SPSS version 23.0 software (SPSS Inc., Chicago, IL, USA).

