## Discussion

AECOPD are important events in the management of COPD because they negatively impact health status and rates of hospitalization and readmission, and potentially result in death and functional disability [22, 23]. The goals of treatment for AECOPD are to minimize the negative impact of the current exacerbation and prevent the development of subsequent events. The chemical medications most commonly used for AECOPD are bronchodilators, corticosteroids, and antibiotics. CM is used extensively in the treatment of AECOPD in Asia, particularly in China. The effects of CM, especially herbal medicines, in improving respiratory symptoms and decreasing the incidence of COPD exacerbations are well known.

Clinical studies have postulated that herbal medicine is effective as a supplemental remedy for treating AECOPD [8, 24]. However, due to the single type of syndrome, limited sample sizes, or methodological problems apparent in some studies, the evidence for the effectiveness of CM was not robust. This RCT will investigate the effectiveness of CM in the treatment of AECOPD. We are attempting to conduct a clinical RCT with adequate design and few deficits. We performed a multicenter, randomized, double-blind, placebo-controlled clinical trial to assess the beneficial or harmful effects of CM for treating AECOPD.

An exacerbation of COPD is defined as an acute worsening of respiratory symptoms that result in additional therapy. The key symptom of an exacerbation is increased dyspnea. Other symptoms include increased sputum purulence and volume, together with increased coughing and wheezing [25]. We thought that if CM is effective in reducing increased dyspnea, cough, and sputum caused by exacerbation, it may primarily affect the respiratory symptoms, so we consider this as the primary outcome of our trial. We also examine the incidence of treatment failure and intubation, length of hospital stays, readmission due to exacerbation, number of deaths, and quality of life to obtain more evidence for AECOPD with CM. Therefore, we hope this trial will provide useful evidence for developing a therapeutic schedule with CM for patients with AECOPD.

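### The CM arm combines three granules assigned by syndrome, but the sample size and named tests address only the pooled contrast, which alone cannot attribute benefit or harm to any one granule

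*Protocol article*

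**What the plan says.** The Participants section admits patients with any one of three syndromes and, as printed, sets no limits on the mix. The Chinese medicine section then gives each syndrome its own product: "Sanhanhuayin granules are given for the syndrome of external cold and internal fluid, Qingrehuatan granules for the syndrome of phlegm-heat congesting the lung". The third syndrome, phlegm-damp, has a product of its own as well (Zaoshihuatan). The Abstract adds that placebo, too, is given by syndrome.

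The objective names no product. It is "to test the clinical efficacy of CM for patients with" AECOPD, together with the safety of CM. The Sample size section plans for a single two-group CAT comparison in which "the clinically meaningful difference (δ) is 2", giving 170 evaluable and 189 enrolled per arm. Statistical analysis lists the t test, rank sum test, chi-squared test and repeated measures ANOVA. It provides one conditional adjustment, by CMH or ANCOVA, which starts "If the effect of the different centers is significant". Syndrome, which decides the product a patient receives, has no stated role there.

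The Discussion says that earlier evidence was not robust, "due to the single type of syndrome, limited sample sizes, or methodological problems apparent in some studies".

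**The concern.** The pooled CM effect is an average of three product effects, weighted by whatever syndrome mix is enrolled. Very different patterns can give the same average. A positive result that comes mainly from one granule could be read as support for all three, and a useful granule could be hidden by less useful ones.

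The same applies to harms. An adverse reaction specific to one granule is diluted about threefold if events are pooled over three equally used products.

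The trial is meant to inform a treatment schedule made up of these three products, so a reader will want to know what the data say about each. If by-syndrome results are first produced after the pooled result is known, they will look post hoc.

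**Working it through.** **Inputs.** From Sample size: two-sided α 0.05, power 90%, δ = 2, 10% dropout. Two sets of SDs appear there. The cited result is "the average CAT score of AECOPD patients treated by CM is 16.54 ± 5.50 and that of the placebo is 18.33 ± 5.87". The formula inputs are "The standard deviation of the first group (σ_1_) is 5.50 and that of the second group (σ_2_) is 5.78". The syndrome split is not given, so equal thirds is assumed and a range is shown.

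**Reproducing the planned size.** n = (1.96 + 1.28)² × (σ₁² + σ₂²)/δ².
- With 5.50 and 5.78: 10.4976 × 63.6584/4 = 167.1, so 168 per arm.
- With 5.50 and 5.87: 10.4976 × 64.7069/4 = 169.8, so 170 per arm, the printed figure.
- 170/0.9 = 188.9, so 189 per arm and 378 in total.

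The planned size therefore reproduces, for the pooled contrast. At 170 per arm with SDs 5.50 and 5.78, power for 2 points is 90%.

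**Precision by syndrome.** Half-width = 1.96 × √((σ₁² + σ₂²)/n).
- Pooled, n = 170: 1.20 with σ₂ = 5.78; 1.21 with 5.87.
- One syndrome, n = 57 (170/3 = 56.7): 2.07 with σ₂ = 5.78; 2.09 with 5.87.

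The choice of SD does not matter here. With σ₂ = 5.78, the results by share of patients in a syndrome are:

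| Share | Evaluable per arm | 95% CI half-width | Power for 2 points |
|---|---|---|---|
| 10% | 17 | 3.8 | 18% |
| 20% | 34 | 2.7 | 31% |
| 30% | 51 | 2.2 | 43% |
| One third | 56.7 | 2.1 | 47% |
| 50% | 85 | 1.7 | 64% |
| 60% | 102 | 1.5 | 72% |

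**What the pooled test can distinguish.** In equal thirds, true effects of (2, 2, 2), (4, 2, 0), (3, 3, 0) and (6, 0, 0) points all average 2, so each gives the same 90% power. If two granules give 2 points and one gives none, the average is 4/3 = 1.33 and pooled power falls to 59%. These patterns are illustrations; nothing in the article suggests that any granule is inert.

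**What an interaction test could add.** The variance of one within-syndrome difference is 63.6584/56.7 = 1.12. The 2-df non-centrality is Σ(eᵢ − ē)²/1.12.
- (4, 2, 0): 8/1.12 = 7.1, power 66%.
- (3, 3, 0): 6/1.12 = 5.3, power 53%.
- (2, 2, 0): 2.67/1.12 = 2.4, power 26%.

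Such a test is informative only for large differences between granules, so it belongs with the estimates and not among confirmatory tests.

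**Harms.** With zero events, the upper 95% limit is about 3/n, or exactly 1 − 0.05^(1/n).
- All 189 CM patients: 1.6% either way.
- 63 users of one granule (189/3): 3/63 = 4.8%, or 4.6% exactly.

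These counts include every patient allocated to CM. The article assigns safety to the per-protocol set, which would be smaller and would raise both limits.

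**The case against.** A strong defence is available, and much of it stands.

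- *The pooled test is legitimate.* The article describes granules chosen by syndrome, and one overall comparison is a proper test of such a strategy. This stands. The hope of informing a CM schedule is consistent with it, since a schedule that picks the granule by syndrome is what is being tested. A reader might infer a contradiction with the trial's aim, but there is none.
- *The data can speak to each granule.* A reader might infer that the trial cannot show which product works or is safe. The documents do not support that. Syndrome is an entry criterion and placebo is given by syndrome, so each granule has its own concurrent randomized controls. Within-syndrome estimates are valid, only imprecise.
- *The Discussion remark commits the trial to nothing.* A reader might say that criticising single-syndrome studies obliges this trial to test each syndrome. Enrolling three syndromes already widens the population, which is a fair response to that limitation.
- *Silence is not an error.* The strata are not named and syndrome may be among them. The full protocol and analysis plan may contain by-syndrome analyses, and their absence from an article is not a defect. This also stands. The point rests on what the article does state: three products, one sized contrast, and a list of tests and one adjustment in which syndrome has no place.
- *The split and effect patterns are assumed.* That is true, and it is why a range is shown. At every share in the table, the by-syndrome estimate is less precise than the pooled one.

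**Conclusion.** The point holds as a limit on interpretation that the stated analysis leaves unaddressed. It does not invalidate the design. The trial is sized, and its named tests are described, only for pooled CM versus placebo. That contrast supports a conclusion about syndrome-guided treatment and, by itself, none about an individual granule.

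Under equal thirds, a by-syndrome CAT difference is known to within about ±2.1 points, roughly the size of the 2-point effect that the trial is planned to detect, against ±1.2 pooled. Power for 2 points within one syndrome is about 47%. Zero events on one granule leaves rates up to about 4.6 to 4.8% open, against 1.6% for the arm as a whole. All by-syndrome figures depend on the assumed split. For shares from 10% to 60%, the half-width runs from 3.8 to 1.5 points.

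These figures do not call for a larger trial or separate confirmatory tests. They show why by-granule results should be planned as estimates and worded with care.

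**What to change.** - Keep pooled CM versus placebo as the primary contrast, and limit the confirmatory conclusion to the syndrome-guided strategy.
- Include baseline syndrome as a factor in the primary CAT model, regardless of whether the centre effect is significant.
- Before unblinding, pre-specify the CAT difference with 95% CI for each syndrome and its granule, and a treatment-by-syndrome interaction, labelled as estimation only. Because the article excepts data analysts from blinding, this should be fixed before anyone examines outcomes by arm.
- Tabulate adverse events by granule against placebo patients with the same syndrome.
- If the full analysis plan already contains these items, only the wording of the claim needs aligning.

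The cost is some wording, one additional factor in the model and a few tables. Syndrome is already determined at entry, so no new data are needed, and completed recruitment is no obstacle. The drawbacks are that the per-granule estimates will be imprecise and the headline claim narrower.

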### Combination therapy

During the treatment period, if there is comorbidity, certain symptomatic treatments can be given according to specific clinical conditions, but it is forbidden to use traditional CM or Chinese patent medicines that provide results similar to the research effect. Drugs for coronary heart disease, diabetes, and hypertension are all prescribed according to the guidelines for the disease. The name, manufacturer, batch number, usage, dosage, etc., of the drug will be recorded in detail.

### Outcomes

#### Primary outcome: COPD Assessment Test (CAT)

The primary outcome of this study will be changes in the CAT between baseline, 14 days after treatment, and the 28 and 42 days follow-ups. We will use the CAT to evaluate the impact of AECOPD on a person’s life and how this changes over time.

The CAT is an 8-item questionnaire designed to assess and quantify health-related quality of life and symptom burden in patients with COPD [10, 11]. Each questionnaire item is presented as a semantic 6-point (0–5) differential scale, providing a total score out of 40. Scores of 0–10, 11–20, 21–30, 31–40 represent mild, moderate, severe, or very severe clinical impact, respectively [12]. Evidence has shown the CAT may also prove useful in clinical trials to objectively assess the ability of novel interventions to reduce AECOPD severity [13], and it is a potentially useful instrument to assess the efficacy of treatments following COPD exacerbations [14].

#### Secondary outcomes

The secondary outcomes are described as follows:
Treatment failure rate: Treatment failure is defined as a worsening of symptoms and signs or death [15]. The outcome is the treatment failure rate on day 14 after admission.Treatment success rate: Treatment success is defined as cure (a complete resolution of signs and symptoms associated with the exacerbation) or improvement (a resolution or reduction of the symptoms and signs associated with the exacerbation, without new symptoms or signs) [15]. The outcome is the treatment success rate on day 14 after admission.Length of hospital stay: The length of hospital stay will be recorded at 14 days of the treatment phase.Readmission due to AECOPD: The number of readmissions due to AECOPD will be recorded in the 28-day follow-up period.Intubation rate: The number of intubations will be recorded during hospitalization and in the 28-day follow-up period.Mortality: The number of deaths will be recorded during hospitalization and in the 28-day follow-up period.Dyspnea: The Modified British Medical Research Council (mMRC) questionnaire [16] was considered adequate for assessment of dyspnea, as the mMRC relates well to other measures of health status [17] and predicts future mortality risk [18]. It will be completed and recorded at days 0, 4, 7, 10, and 14 of the treatment phase and at days 28 and 42 of the follow-up phase.Quality of life: The Chinese version of the 36-item Short Form Health Survey (SF-36) [19] and COPD patient-reported outcome scale (COPD-PRO) [20] will be adopted to assess the health-related quality of life of patients with AECOPD.The SF-36 contains eight domains: physical function, restrictions in activity due to physical problems, bodily pain, general health, vitality, social function, restrictions in activity due to emotional problems, and mental health. The COPD-PRO has inherent correlation with the evaluation of efficacy of CM based on clinical symptoms. It contains 17 items in three domains: amelioration of clinical symptoms, satisfaction of health condition, and satisfaction of treatment effect [20].

Each participant will be assessed by the investigator at baseline, 14 days after treatment, and at the 28 days and 42 days follow-ups.

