**Fig. 1 Fig1:**
[figure not shown]
Flowchart for the intervention trial

**Table 1 Tab1:** Timing of treatment visits and data collection

	Baseline	Treatment phase				Follow-up phase	
	Day 0	Day 4	Day 7	Day 10	Day 14	Day 28	Day 42
	V1	V2	V3	V4	V5	V6	V7
Sign informed consent	×						
Randomization	×						
Medical history	×						
Intervention	×	×	×	×			
Primary outcome							
CAT	×				×	×	×
Secondary outcomes							
Treatment failure		×	×	×	×		
Length of hospital stays					×		
Readmission due to AECOPD						×	×
Intubation rate		×	×	×	×	×	×
Mortality		×	×	×	×	×	×
mMRC	×	×	×	×	×	×	×
SF-36	×				×	×	×
COPD-PRO	×				×	×	×

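### Hospital outcomes are badly fixed in time: stay has no value past Day 14, readmissions before Day 14 fall outside the count, and failure and success are dated from admission rather than randomisation

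*Protocol article*

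**What the plan says.** All statements are in the protocol article.

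- **Length of stay** (Secondary outcomes): "The length of hospital stay will be recorded at 14 days of the treatment phase". In Table 1 the row "Length of hospital stays" has a single mark, at Day 14 (V5).
- **Readmission** (Secondary outcomes): "The number of readmissions due to AECOPD will be recorded in the 28-day follow-up period". In Table 1 the row "Readmission due to AECOPD" is marked only at Day 28 (V6) and Day 42 (V7).
- **Intubation**, for contrast: "The number of intubations will be recorded during hospitalization and in the 28-day follow-up period". Mortality has the same two-part window. Table 1 marks both from Day 4 to Day 42.
- **Treatment failure**: "The outcome is the treatment failure rate on day 14 after admission". **Treatment success**: "The outcome is the treatment success rate on day 14 after admission".
- **Clock**: Table 1 puts baseline and randomisation at Day 0, and the granules are given for 14 days (Chinese medicine section).
- **Setting** (Participants): patients "will be screened in the outpatient and inpatient wards". None of the listed inclusion criteria is admission to hospital, and none ties randomisation to the day of admission.

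**The concern.** Each of these outcomes needs a start, an end and a set of patients to whom it applies. Here one of the three is missing or does not match the trial's own schedule.

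A stay that continues past V5 is recorded while still incomplete. If the stay to date is used, long stays are shortened, and the difference in mean days between arms with them.

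Readmission can happen as soon as a patient has gone home, but counting starts only when treatment ends. The first two weeks are left out, and the arm that discharges earlier would have more uncounted time at risk.

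Failure and success are tied to an event, admission, that need not coincide with randomisation and that the criteria do not require.

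Four secondary outcomes are affected. The Discussion names failure, stay and readmission among those meant to add evidence beyond the primary outcome, so their definitions should not depend on how a site reads them.

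**Working it through.** The plan gives no figure for stay, readmission, failure or success, so there is none to reproduce. The first, third and fourth steps set the statements side by side. The second is an illustration on assumed inputs.

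**1. Stay.** Text and Table 1 agree on one recording, at Day 14. Visits continue to Day 42, but stay is not marked at them. A patient in hospital at V5 therefore has a known stay to date and no recorded end.

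**2. Size if the stay to date is used.**

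Assumptions, none of them from the documents: log-normal stay with control mean m and SD s; enrolment on the day of admission; treated stay equal to control stay times (m − 1.5)/m, a true difference of 1.5 days; stays over 14 days read as 14. From the Sample size section: 170 evaluable patients per group, here all taken as hospitalised.

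Formulas, with Φ the standard normal distribution function:
- σ² = ln(1 + (s/m)²) and μ = ln m − σ²/2
- share over 14 days = 1 − Φ((ln 14 − μ)/σ)
- mean of the capped stay = m·Φ((ln 14 − μ − σ²)/σ) + 14·[1 − Φ((ln 14 − μ)/σ)]
- expected z = difference / √((SD₁² + SD₂²)/170)

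| m, s | Control stays over 14 days | Capped means, control and treated | Capped difference | z uncapped | z capped |
|---|---|---|---|---|---|
| 10, 4 | 14% | 9.52 and 8.31 | 1.22 | 3.73 | 3.82 |
| 12, 6 | 29% | 10.45 and 9.56 | 0.89 | 2.45 | 2.50 |
| 14, 6 | 42% | 11.72 and 11.01 | 0.71 | 2.43 | 2.36 |

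For m = 12, s = 6, the uncapped SDs are 6 and 6 × 10.5/12 = 5.25, so z = 1.5/√((36 + 27.56)/170) = 2.45. The capped SDs are 3.21 and 3.32, so z = 0.885/√((10.29 + 11.01)/170) = 2.50. The cap lowers the difference and the spread together. The effect in days is understated, and the chance of detecting it hardly moves.

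**3. Readmission.** The window is Days 14 to 42 in both text and table. A patient discharged on Day 6 and readmitted on Day 11 is not counted. For a discharge on Day x before Day 14, the uncounted time is 14 − x days. On the assumptions of step 2, its mean in the control arm is 14 minus the capped mean: 4.48, 3.55 and 2.28 days. The treated arm has 1.22, 0.89 and 0.71 days more. With equal discharge times the arms lose the same amount. The documents give no early readmission rate, so the number of missed events cannot be worked out.

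**4. Failure and success.** For an inpatient randomised d days after admission, day 14 after admission is trial Day 14 − d. With d = 3, for illustration, that is Day 11: between V4 (Day 10) and V5 (Day 14), with no visit and three days of treatment to go. For a patient never admitted, the date does not exist.

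**The case against.** The strongest reply is that the text says when a field is filled in, not how an unfinished stay is scored. No sentence sets long stays to 14 days, and the case report form or the analysis plan may hold a rule. That stands: a reader might infer a cap, but the documents do not state one, so the shrinkage in days is conditional. What the reply does not remove is that both text and table stop recording stay at Day 14 while visits go on to Day 42.

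A reader might also infer a loss of power for stay. The calculation does not show one.

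For readmission, a fixed window after treatment is the same for both arms and is stated consistently. Some early relapses would also appear as treatment failure, assessed from Day 4, or as adverse events. It would go too far to say that the count is biased between arms, since that needs a difference in discharge time, which is not known. But neither failure nor an adverse event is a readmission count, and the wider window given to intubation and mortality shows that the in-hospital period could have been included.

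On setting, the text says where patients are screened. It does not say that anyone is treated as an outpatient, and much of the outcome wording presumes a hospital stay. Reading the trial as enrolling unadmitted outpatients who contribute zeros goes beyond the documents. It is only a possibility that no criterion closes.

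Finally, admission may be loose wording for trial entry, and the failure marks in Table 1, which end at V5, give a workable reading. That is a good reason to write it down.

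**Conclusion.** The point holds for four secondary outcomes, as faults of definition.

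- **Stay** has no final value for patients still in hospital at Day 14. If the stay to date is used, a true 1.5-day difference would read as about 0.7 to 1.2 days, with expected z nearly unchanged. This rests wholly on the assumed distributions and on the assumed cap.
- **Readmissions** before Day 14 are not counted. The gap is certain from text and table. Its size is unknown, and it is uneven between arms only if discharge times differ.
- **Failure and success** carry a time origin that does not match the trial clock and is undefined for anyone not admitted.

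The primary CAT outcome and the planned 378 patients are not touched. The changes should be made, but they do not threaten the main conclusion.

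**What to change.** 1. **Stay.** Take the actual discharge date up to Day 42, at V6 and V7 or from hospital records for patients already past those visits. Analyse stay in patients hospitalised at baseline, in a way that does not let an in-hospital death count as a short stay; time from randomisation to discharge alive is one option.
2. **Readmission.** Count AECOPD readmissions over one common window, from randomisation to Day 42, in the same patients. A count starting at each patient's first discharge would give unequal time at risk, so the common window is preferable. Report any never-admitted patients separately.
3. **Failure and success.** Date both at Day 14 after randomisation, which is V5.

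The trial status section says that recruitment is complete, so the definitions should be settled before treatment codes are released for analysis.

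The cost is one extra date field and some record retrieval. If unadmitted outpatients were enrolled, the denominators for stay and readmission become smaller.
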